#### *Gastrointestinal*

- Gastrointestinal bleed, requiring treatment
- Liver failure, defined as INR  $\geq 1.5$  not corrected by parenteral administration of vitamin K [47], or AST or ALT  $\geq 950$  IU/L [48]
- Necrotising enterocolitis: systemic and abdominal signs consistent with necrotising enterocolitis, with or without radiological signs, and commenced on treatment by a paediatric surgery specialist [3].
- Oesophageal or bowel perforation, not associated with necrotising enterocolitis
- Other gastrointestinal

#### *Infection*

- Blood stream infection, including both catheter and non-catheter related, with systemic signs of infection, a positive culture not judged to be a contaminant, and for catheter-related, positive cultures from the line or line tip [3]
- Empyema
- Endocarditis, based on diagnostic clinical, imaging or culture evidence
- Gastroenteritis
- Pneumonia, requiring treatment
- Surgical site infection, superficial
- Urinary tract infection
- Other infection not requiring expedited reporting

#### *Other complication*

- Readmission to ICU, any cause
- Other not requiring expedited reporting

## 9.6 Events that require expedited reporting to the Sponsor on the SAE Form

Based on those morbidities identified as important in the recent multi-centre UK study [3], the following SAEs are protocol-defined as expected but must be reported in an expedited manner using the Serious Adverse Event reporting form to enable efficient monitoring of frequency of events; this requirement has been agreed with the DMC prior to commencing recruitment:

- **Death**
- **Extracorporeal life support (ECLS):** Use of extracorporeal support following the index operation, whether started in the operating theatre or in the ICU, and whether the indication was cardiac arrest, low cardiac output state, poor cardiac function, arrhythmia, residual or recurrent cardiac lesion, or sepsis.
- **Major adverse cardiac event:** Includes cardiac arrest, where the child receives any chest compressions or defibrillation; chest reopening on the ICU or ward, for any reason; major haemorrhage in the ICU following surgery, defined as >10ml/kg/hr for 2 consecutive hours; and acute shunt failure, in those with a surgically constructed systemic to pulmonary shunt.
- **Unplanned reoperation/intervention in the early postoperative period:** Cardiac surgical operations with or without cardiopulmonary bypass, or interventional catheter procedures that occur within 30 days after the index operation or within the same hospital admission, not intended during the planning phase. Includes diaphragm plication and pacemaker insertion for surgically acquired arrhythmias but excludes planned diagnostic or interventional cardiac catheterisation, delayed chest closure, procedures for bleeding, institution of or weaning from ECLS, and non-cardiac surgical operations.
- **Acute neurological event:** New abnormality detected on clinical evaluation: coma; intracranial haemorrhage or stroke (confirmed on imaging); seizures (confirmed on electroencephalogram or obvious motor signs); or other neurological injury likely to result in a persistent or permanent deficit.
- **Sepsis:** defined broadly as severe infection leading to life-threatening organ dysfunction
- **Deep surgical site infection:** Surgical site infection and/or mediastinitis including any infection of an incised wound that undergoes any surgical reintervention within 30 days after the index operation or within the same hospital admission, independent of culture positivity.
- **Other severe or life-threatening unexpected event:** Any other events which are severe or life-threatening must be formally assessed for relatedness (PI) and expectedness (CI).

If a patient fulfils more than one of the above SAE criteria, e.g. cardiac arrest requiring ECLS, a separate SAE form should be completed for each of the events.

The following events were classified as important morbidities but will not require expedited reporting: blood stream infection or endocarditis; feeding problems; necrotising enterocolitis; need for renal replacement therapy; and prolonged pleural effusion or chylothorax [3].

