| Serious Adverse Event                         | SAE   | Any untoward medical occurrence or effect that: 
 
• Results in death or is life-threatening
 
• Requires hospitalisation or prolongation of existing hospitalisation
 
• Results in persistent or significant disability or incapacity
 
• Is a congenital anomaly/birth defect
 
• Or is otherwise considered medically significant by the Investigator
 
 |
| Serious Adverse Reaction                      | SAR   | An Adverse Reaction which also meets the definition of a Serious Adverse Event                                                                                                                                                                                                                                                                                                                                                                               |
| Unexpected Adverse Reaction                   | UAR   | An AR, the nature or severity of which is not consistent with the applicable product information (e.g. Investigator Brochure for an unapproved IMP or (compendium of) Summary of Product Characteristics (SPC) for a licensed product). When the outcome of an AR is not consistent with the applicable product information the AR should be considered unexpected.                                                                                          |
| Suspected Unexpected Serious Adverse Reaction | SUSAR | A SAR that is unexpected i.e. the nature, or severity of the event is not consistent with the applicable product information. A SUSAR should meet the definition of an AR, UAR and SAR.                                                                                                                                                                                                                                                                      |

**Table 4.** Definitions of types of adverse events.

 The term life-threatening is defined as diseases or conditions where the likelihood of death is high unless the course of the disease is interrupted.

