## 9.2 Adverse Events - General Recording Requirements

The collection and reporting of Adverse Events (AEs) will be in accordance with the UK Policy Framework for Health & Social Care (2017), the requirements of the Health Research Authority (HRA), and the sponsor's Code of Practice for Research. Definitions of the different types of AEs are listed in table of definitions, section 9.1.

It is routine practice to record adverse events in the patient's medical notes and it is also recommended that this includes the documentation of the assessment of severity and seriousness, and for causality (relatedness) in relation to the intervention(s) in accordance with the protocol. The assessment of causality should be made with regards to the Reference Safety Information (RSI). For the purposes of the DESTINY trial, this will be the Investigator Brochure for del Nido cardioplegia and the Summary of Product Characteristics for St Thomas' cardioplegia.

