### 9.7.3 Assessment of relatedness

When completing the SAE form, the PI will be asked to define the causality (relatedness) and the severity of the AE. In defining the causality, the PI must consider if any concomitant events or medications may have contributed to the event and, where this is so, these events or medications should be reported on the SAE form. It is not necessary to report concomitant events or medications which do not contribute to the event. The assessment of relatedness is depicted in **Table 5**.

| Category    | Definition                                                                                                                                                                                                              | Causality |
|-------------|-------------------------------------------------------------------------------------------------------------------------------------------------------------------------------------------------------------------------|-----------|
| Definitely  | There is clear evidence to suggest a causal relationship, and other possible contributing factors can be ruled out.                                                                                                     | Related   |
| Probably    | There is evidence to suggest a causal relationship, and the influence of other factors is unlikely.                                                                                                                     |           |
| Possibly    | There is some evidence to suggest a causal relationship. However, the influence of other factors may have contributed to the event (e.g. the participant's clinical condition, other concomitant events, or medication) |           |
| Unlikely    | There is little evidence to suggest there is a causal relationship. There is another reasonable explanation for the event (e.g. the participant's clinical condition, other concomitant events, or medication).         | Unrelated |
| Not related | There is no evidence of any causal relationship.                                                                                                                                                                        |           |

**Table 5.** Assessment of relatedness.

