## 9.8 Assessment of Expectedness by the CI

The CI will also assess all related SAEs for expectedness with reference to the following criteria (**Table 6**).

| Category   | Definition                                                                                                                                                                                                                                                                        |
|------------|-----------------------------------------------------------------------------------------------------------------------------------------------------------------------------------------------------------------------------------------------------------------------------------|
| Expected   | An adverse event that is consistent with known information about the trial related procedures or that is clearly defined in the relevant safety information: DESTINY Investigator Brochure del Nido (v1.0, 30/03/2021) and SmPC Martindale Cardioplegia Concentrate (18/02/2015). |
| Unexpected | An adverse event that is not consistent with known information about the trial related procedures.                                                                                                                                                                         |

**Table 6.** Assessment of expectedness.

The CI will not overrule the severity or causality assessment given by the site PI but may add additional comment on these. If the event is unexpected (i.e. is not defined in the protocol as

an expected event or is not defined in the approved version of the RSI, it will be classified a Suspected Unexpected Serious Adverse Reaction (SUSAR).

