## **9.10 Reporting SAEs to third parties**

### **9.10.1 Reporting to the Competent Authority and main Research Ethics Committee**

A minimal data set of all individual events categorised as a fatal or life threatening SUSAR to the Medicines and Healthcare products Regulatory Agency (MHRA), main REC and Research Governance Team (RGT) by BCTU within 7 days. Detailed follow-up information will be provided within an additional 8 days. All other events categorised as non-life threatening SUSARs will be reported within 15 days.

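### Section 9.6 reports unlisted events by severity, not seriousness, and the open lines in 9.5 take the rest, so some unlisted SAEs have no required route to expectedness review

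*Protocol*

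**What the plan says.** **Definition.** Table 4 in section 9.1 defines an SAE by five seriousness criteria: death or threat to life, hospitalisation ("Requires hospitalisation or prolongation of existing hospitalisation"), disability, congenital anomaly, and medical significance in the investigator's view. Section 9.2 recommends "the documentation of the assessment of severity and seriousness" in the medical notes, so the protocol treats the two as different attributes.

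**Expedited list.** Section 9.6 opens with "the following SAEs are protocol-defined as expected but must be reported in an expedited manner". It names seven kinds of event and closes with one residual item, labelled "Other severe or life-threatening unexpected event". The sentence under that label is "Any other events which are severe or life-threatening must be formally assessed for relatedness (PI) and expectedness (CI").

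**Non-expedited list.** Section 9.5 lists events by organ system and ends most systems with an open residual line. Everything in 9.5 counts as expected by protocol, is handled as a complication and is recorded on the Postoperative CRF.

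**What follows the form.** Under 9.7.3, when the SAE form is completed, "the PI will be asked to define the causality (relatedness) and the severity of the AE". Receipt of the form starts the Chief Investigator's review. Section 9.8 states: "The CI will also assess all related SAEs for expectedness". Section 9.10.1 states: "All other events categorised as non-life threatening SUSARs will be reported within 15 days".

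**The concern.** Severity describes how intense an event is; seriousness describes its consequence. A moderate event can keep a child in hospital longer, or be medically significant, and so be an SAE by Table 4 without being severe. If the only residual route onto the SAE form asks about severity, such an event can be handled fully in line with the protocol and still receive no reported relatedness judgement and no expectedness judgement.

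That matters because a SUSAR can arise from any seriousness criterion, and sections 9.8 and 9.10.1 both assume that SUSARs which are not life-threatening will be identified. The risk assessment in section 3.1.4 records that the product is not licensed in the EU, although the same sentence cites extensive clinical evidence in this patient group. The residual category is where a reaction that nobody listed in advance would have to appear.

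The word *unexpected* in the label adds a second, smaller problem. It sits in a list introduced as expected events, and it names a judgement that 9.8 gives to the Chief Investigator once the form has arrived.

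**Working it through.** No figure is involved. The check follows one type of event through the protocol: an event not specifically named in 9.5 or 9.6, serious because it prolongs hospitalisation or is medically significant, not severe and not life-threatening.

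1. **Is it an SAE?** Yes. Table 4 needs only one criterion, and severity is not among them.
2. **Does 9.6 require an SAE form?** No. It is none of the named events. The residual item covers "Other severe or life-threatening unexpected event", and the event is neither severe nor life-threatening.
3. **Where does it go?** To a residual line in 9.5. Six of the seven headings there have one: cardiovascular, respiratory, neurological, gastrointestinal, infection and other complication. The renal heading has none. Four of the six are limited to events that do not need expedited reporting, which refers the reader back to 9.6, where the event did not qualify. The respiratory and gastrointestinal lines have no such limit.
4. **Which form carries it?** The Postoperative CRF, due at hospital discharge (10.2). The SAE form is tied to SAEs that need expedited reporting (9.7.1, 10.2).
5. **Is relatedness reported?** Not by any stated step. The investigator's causality statement is made on the SAE form (9.7.3). Sections 9.2 and 9.3 recommend recording causality in the notes or source data, but do not send it on. The CRF itself is not shown, and the protocol describes no relatedness question on it.
6. **Does the Chief Investigator review it?** Not by any stated step, because that review starts on receipt of an SAE form (9.7.3).
7. **Can it be classified as unexpected?** Section 9.8 looks to whether the event is defined as expected in the protocol or the reference safety information. Placement under 9.5 already makes it expected by protocol, so the placement works against a SUSAR classification.
8. **Does the DMC see it as an SAE?** Section 9.10.2 limits its SAE review, apart from deaths and life-threatening SUSARs, to SAEs that need expedited reporting.

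Set against the later sections:

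| Section | Scope promised | Reached by this event? |
|---|---|---|
| 9.8 | "The CI will also assess all related SAEs for expectedness" | No required route, even if related |
| 9.10.1 | "All other events categorised as non-life threatening SUSARs will be reported within 15 days" | No required route |

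**The label.** The introduction to 9.6 says "the following SAEs are protocol-defined as expected but must be reported in an expedited manner", yet the last item is headed as unexpected. The two cannot both describe the same item. The sentence under the label does not repeat the word and leaves expectedness to the Chief Investigator, in line with 9.8. The inconsistency therefore lies in the label.

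**The case against.** The strongest defence is that targeted reporting is deliberate. Sections 9.3 and 9.4 explain that events normally classed as serious are common after these operations and that full reporting would bury the critical ones. Section 9.6 says its requirement was agreed with the DMC before recruitment. Section 9.4 also says that local teams collect data on all events meeting the SAE definition. This stands as a reason to exempt the anticipated events named in 9.5, and it means the events in question are not lost to the trial. It does not explain why an unlisted, possibly related SAE should lack a causality and expectedness step that 9.8 says it will have.

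Several stronger readings are tempting and are not supported:

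- **That such an event can never become a SUSAR.** *Severe* is not defined, and a site may read it as *serious* and report. The accurate statement is that no route is required.
- **That severity is judged only once the form exists.** Sections 9.2 and 9.3 recommend recording it in the notes and source data, so a site can apply that test beforehand.
- **That *unexpected* is a firm entry condition.** It appears only in the label.
- **That all seriousness criteria other than death or threat to life are uncovered.** The named items in 9.6 must be counted too. Its acute neurological item covers much of the disability criterion, congenital anomaly has little practical bearing here, and many causes of a prolonged stay are named in 9.5 or 9.6. What remains is mainly hospitalisation and medical significance.
- **That the number of missed events can be estimated.** The protocol gives no rate for unlisted, non-severe SAEs, and only related and unexpected ones could become SUSARs.

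**Conclusion.** The point holds as a narrow internal contradiction in safety reporting. Section 9.6 uses severity where Table 4 uses seriousness, the residual lines in 9.5 class what is left as expected, and together they fail to deliver the scope promised in 9.8 and 9.10.1. The size is limited to unlisted SAEs that are serious mainly through prolonged hospitalisation or medical significance and that a site does not regard as severe. Their number cannot be derived from the protocol, and the conclusion does not need it. The label's *unexpected* is a secondary inconsistency.

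The conclusion assumes that *severe* carries its usual meaning of intensity, as the separate mention of seriousness in 9.2 suggests, and that the Postoperative CRF carries no relatedness step beyond what the protocol describes. The change should be made: it closes a gap in safety review at little cost.

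**What to change.** 1. Reword the last item of 9.6 along these lines: *Any other event that meets the SAE definition in Table 4 and is not specifically named in 9.5 or above must be reported on the SAE form.*
2. Remove *unexpected* from its label, and word the introduction to 9.6 so that it does not describe this item as expected.
3. State in 9.5 that its residual *Other* lines do not count as named events. Without this, a site could still file the event there and send no form.
4. Leave severity and causality with the PI and expectedness with the Chief Investigator, as in 9.7.3 and 9.8. Leave the specifically named exemptions in 9.5 as they are.

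If the full change is thought too broad, the minimum is that any unlisted SAE the PI considers possibly, probably or definitely related (the three categories that Table 5 counts as related) goes on the SAE form.

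The cost is a few sentences in the next amendment, a note to sites and a few extra SAE forms.

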## 9.7 Reporting procedure

### 9.7.1 Reporting procedure for expedited SAEs by sites

On becoming aware that a participant has experienced an expedited SAE, the Investigator or suitably medically qualified delegate should report it to their own Trust in accordance with local practice and to the BCTU trials office as per section 9.6 above.

To report an expedited SAE to the BCTU trials office, the Investigator or delegate must complete, date, and sign the trial-specific SAE form. The completed form together with any other relevant, appropriately anonymised data should be scanned and sent as email attachments to [[contact]](mailto:[contact]) no later than 24 hours after first becoming aware of the event:

Where an SAE Form has been completed by someone other than the Investigator or delegate, initially, the original SAE form will need to be countersigned by the Investigator to confirm agreement with the causality and severity assessments.

On receipt of an SAE form, the BCTU trials team will transcribe the data onto the trial database. This results in a unique reference number being generated for the SAE, which the BCTU trials team will share with the site via email as proof of receipt of the SAE form. The site and the BCTU trials team should ensure that the SAE reference number is quoted on all correspondence and follow-up reports regarding the SAE and filed with the SAE in the Site File.

If the site has not received confirmation of receipt of the SAE from BCTU or if the SAE has not been assigned a unique SAE identification number within 1 working day, the site should contact the BCTU trials team.

### 9.7.2 Provision of follow-up information

Following the reporting of an SAE for a participant, the participant should be followed up until resolution or stabilisation of the event. Follow-up information should be provided using the SAE reference number provided by the DESTINY trial team by completing follow-up SAE reports and sending via email to the trial office. Once the SAE has been resolved, all critical follow-up information has been received and the paperwork is complete, this should be filed in the Site File, whilst BCTU trials office will retain copies.

### 9.7.3 Assessment of relatedness

When completing the SAE form, the PI will be asked to define the causality (relatedness) and the severity of the AE. In defining the causality, the PI must consider if any concomitant events or medications may have contributed to the event and, where this is so, these events or medications should be reported on the SAE form. It is not necessary to report concomitant events or medications which do not contribute to the event. The assessment of relatedness is depicted in **Table 5**.

| Category    | Definition                                                                                                                                                                                                              | Causality |
|-------------|-------------------------------------------------------------------------------------------------------------------------------------------------------------------------------------------------------------------------|-----------|
| Definitely  | There is clear evidence to suggest a causal relationship, and other possible contributing factors can be ruled out.                                                                                                     | Related   |
| Probably    | There is evidence to suggest a causal relationship, and the influence of other factors is unlikely.                                                                                                                     |           |
| Possibly    | There is some evidence to suggest a causal relationship. However, the influence of other factors may have contributed to the event (e.g. the participant's clinical condition, other concomitant events, or medication) |           |
| Unlikely    | There is little evidence to suggest there is a causal relationship. There is another reasonable explanation for the event (e.g. the participant's clinical condition, other concomitant events, or medication).         | Unrelated |
| Not related | There is no evidence of any causal relationship.                                                                                                                                                                        |           |

**Table 5.** Assessment of relatedness.

On receipt of an SAE Form, the Trials Office will forward it, with the unique reference number, to the Chief Investigator (CI) who will independently review the causality of the SAE. An SAE judged by the PI or CI to have a reasonable causal relationship with the intervention will be regarded as a related SAE (SAR). The causality assessment given by the PI will not be downgraded by the CI. If the CI disagrees with the PI's causality assessment, the opinion of both parties will be documented, and where the event requires further reporting, the opinion will be provided with the report. The CI will send their assessment of causality and, where applicable, expectedness (see 9.8 below) to the Trials Office.

